**Methods:**

A multicenter RCT will be conducted among MSM in 8 cities in China. Eligible participants are men aged 18-49 years who self-report ≥2 male sex partners in the past 6 months, predominantly practice insertive anal sex, and are willing to undergo circumcision. Interested men who satisfy inclusion criteria will be tested for HIV 1 month before enrollment and at enrollment, and only those who are HIV negative will be enrolled. At baseline, all enrolled participants will be asked to report sociodemographic characteristics and sexual behaviors; provide a blood sample for HIV, syphilis, and herpes simplex virus type 2 testing; and provide a penile swab for human papillomavirus testing. Participants will be randomly assigned to the intervention or control group. Those in the intervention group will receive VMMC and undergo a web-based weekly follow-up assessment of postsurgery healing for 6 consecutive weeks. All participants will be tested for HIV at 3-, 6-, 9-, and 12-month follow-ups. All participants will also be asked to report sexual behaviors and undergo repeat herpes simplex virus type 2 and human papillomavirus testing at 6- and 12-month follow-ups. The primary end point is HIV seroconversion. Secondary end points are the safety and satisfaction with VMMC and the changes in sexual behaviors after VMMC. The grouped censored data will be analyzed by intention-to-treat approach.

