**Assessments**							
	HIV rapid testing	**√**	**√**	**√**	**√**	**√**	**√**
	Baseline questionnaire		**√**				
	Follow-up questionnaire				**√**		**√**
	STIs screening^b^		**√**		**√**		**√**

^a^For participants in the intervention group, they will be formally enrolled after completing the circumcision. There is a maximum waiting period of 3 months for surgery and a 6-week postoperative recovery period before formal follow-up phase. For participants in the control group, they will remain uncircumcised at enrollment and follow-up, and they will enter the formal follow-up phase after completing the enrollment and baseline questionnaire.

^b^STIs include herpes simplex virus type 2, syphilis, and penile human papillomavirus.

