### Randomization and Follow-Up

Eligible men will be randomized using a 1:1 allocation ratio to the intervention and control groups. Randomization lists for each study site have been pregenerated by researchers. Each envelope with a unique number will be assigned for 1 allocation sequence, into which a card with grouping information will be put before sealing. Trained investigators at each study site will assign an envelope to each participant according to the order of the participant’s arrival. Participants cannot be blinded due to the nature of the intervention. After randomization, trained researchers will provide HIV prevention counseling to participants in both groups, including promotion of consistent condom use and regular HIV testing.

Participants randomized to the intervention group will be encouraged to complete VMMC within 1 week of enrollment. Time to VMMC can be extended up to 3 months after enrollment on a case-by-case basis. We recommend participants to undergo VMMC at a secondary or higher-level medical center of their own choice. Although the clinical VMMC activities are not part of study procedures, a research assistant would accompany the participants to the hospital to undergo the circumcision. This trial will provide a surgical subsidy of CNY 1000 (US $160). If participants do not complete VMMC within 1 month of enrollment, a text message reminder will be sent. The surgeon will check the condition of the foreskin of participants before the operation to determine if surgery is necessary. Men in the intervention group will be advised to abstain from sex for 6 weeks after undergoing VMMC, and the 12-month follow-up period will begin after this 6-week period of abstinence. If men resume sexual behaviors earlier than 6 weeks after VMMC, then the 12-month follow-up period will begin at the time of their first sexual encounter after VMMC.

Men randomized to the control group will complete the baseline survey after enrollment. The 12-month follow-up period for the control group will begin immediately after completing the baseline survey. At the end of the 12-month follow up period, men in the control group will be offered a CNY 1000 (US $160) subsidy to undergo VMMC.

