### Statistical Analysis

All data will be analyzed based on the principle of intention to treat. We will assess the type of missing data and assess attrition effects by testing whether there are systematic differences between dropouts and nondropouts. Key baseline characteristics will be examined between the intervention and control groups to ensure they are balanced; if not, subsequent analyses will assess whether these characteristics are confounding factors of the intervention.

For continuous variables, we will calculate means and SDs, and means will be compared with 2-sample *t* tests or Mann-Whitney tests. For categorical variables, proportions will be compared with chi-square tests or Fisher exact tests. In addition, we assume that HIV status at the end of follow-ups is grouped censored data and suitable for exponential, proportional hazards model with constant baseline hazard. Therefore, differences between the intervention and the control groups will be identified with a Poisson regression model, which includes observed covariates (ie, HIV risk behaviors, such as condom use, number of sexual partners, frequency of insertive anal sex, and HIV-positive sexual partners as well as demographic variables, such as age, education level, and income). Incidence rates will be calculated for each outcome in the 2 groups. Moreover, the incidence rate ratios and their 95% CIs will be estimated using the Poisson regression model. For all the outcome variables, including the primary (ie, HIV incidence) and secondary (ie, penile HPV incidence, clearance and persistent infection, HSV-2 incidence, and syphilis incidence) outcomes of interest, the aforementioned analyses will be repeated across all the visits (ie, 6- and 12-months follow-ups).

The changes in sexual behaviors after VMMC over time between the intervention and the control groups will be compared with the generalized estimating equations. For outcomes of VMMC safety and satisfaction among circumcised MSM, we will perform the same statistical description and comparative analyses described as above.

A 2-sided *P* value lower than .05 will be used to infer statistically significant difference. All the statistical analyses will be performed with R software (version 4.2.1; R Core Team).

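### The protocol contradicts itself on whether baseline data are taken before or after allocation, so reported baseline behavior could be affected by knowing the arm

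*Protocol article*

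**What the plan says.** Four places in the protocol article bear on the order of events.

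- **Abstract, Methods:** "At baseline, all enrolled participants will be asked to report sociodemographic characteristics and sexual behaviors", together with blood and swab samples. Random assignment comes in the next sentence.
- **Randomization and Follow-Up:** after the paragraph on envelopes, lack of blinding and counseling following randomization, the text says "Men randomized to the control group will complete the baseline survey after enrollment", and then "The 12-month follow-up period for the control group will begin immediately after completing the baseline survey". For the other arm it says "Participants randomized to the intervention group will be encouraged to complete VMMC within 1 week of enrollment" and "Time to VMMC can be extended up to 3 months after enrollment on a case-by-case basis".
- **Table 2:** consent, assignment, intervention and the baseline questionnaire all fall in the Month 0 column. Footnote a says: "For participants in the intervention group, they will be formally enrolled after completing the circumcision".
- **Statistical Analysis:** key baseline characteristics are compared between arms, and any imbalance leads to an assessment of confounding. The Poisson model adjusts for HIV risk behaviors, described as observed rather than as baseline values. For the secondary behavioral outcome, "The changes in sexual behaviors after VMMC over time between the intervention and the control groups will be compared with the generalized estimating equations".

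**The concern.** Baseline values serve as a reference only if allocation cannot have influenced them. Here the behavioral items are self-reported, participants know their arm once the envelope is opened, and both arms then receive counseling that promotes condom use. A man who answers after that point may report differently because of the arm he drew or the advice he was given. If the arms also answer at different times after allocation, the effect need not cancel between them.

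Three uses of the data are exposed. A reporting difference caused by allocation could be mistaken for chance imbalance and then adjusted for. The comparison of behavior change, which is how this trial would detect risk compensation, could start from reference values that are not comparable. The adjusted HIV rate ratio could be affected if these values enter the Poisson model. The baseline swab belongs to the same Month 0 visit and is the natural reference for HPV clearance and persistence, so its order matters too.

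**Working it through.** The point turns on sequence, and the plan states no figure to reproduce. The passages are set side by side.

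**1. What enrollment means.** The Interventions section sets the 3-month limit for surgery from randomization. Randomization and Follow-Up sets the same limit from enrollment. The main text thus treats the two as one time point, with surgery afterwards. Table 2, footnote a, places formal enrollment in the circumcision arm after surgery. These two meanings cannot both hold.

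**2. Control arm.** The survey comes after enrollment, and the sentence is about men already randomized. With the main-text meaning from step 1, this puts the survey at or after allocation. The abstract's narrative order puts it before. Table 2 does not decide, because it has one column for everything at Month 0.

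**3. Circumcision arm.** No sentence says when these men complete the baseline survey. The abstract takes baseline data from enrolled participants. Combined with footnote a, that permits a survey after surgery. Combined with the main text, it puts the survey before surgery.

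**4. Possible gap between arms.** If the footnote reading applied, the survey in the circumcision arm could fall anywhere from about 1 week (the encouraged time to surgery) to 3 months (the maximum) after allocation. The article gives no recall window for the survey. Assuming 6 months, as in the eligibility criteria, the share of recalled time after allocation would run from about 1/26 = 4% to 3/6 = 50%. This range is conditional on both assumptions.

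**5. Effect on estimated change.** Let an arm's baseline count be misreported by a fraction d, with accurate follow-up and no true change. The apparent ratio of follow-up to baseline is 1/(1 − d).

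- Assumed under-reporting of 10%: 1/0.9 = 1.11, a spurious rise of about 11%.
- Assumed over-reporting of 10%: 1/1.1 = 0.91, a spurious fall of about 9%.

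The value of d is not in the documents. The formula shows only that an error in one arm's baseline passes almost one for one into that arm's estimated change.

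**The case against.** The strongest reply is that this is loose wording. The phrase about men randomized to control may simply name the arm whose follow-up clock the next sentence defines. Footnote a may be meant to define entry into formal follow-up, not to move the survey. The abstract gives the conventional order, and the fuller protocol behind this article may settle the sequence. Recruitment ended in July 2022, so the order of procedures can no longer be changed.

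Much of this stands. The text never orders counseling against the survey, and never says that circumcised men complete the survey after surgery. The encouraged time to surgery is 1 week, and the 3-month limit is a case-by-case extension. The Statistical Analysis section does not say that the model covariates are baseline values. That baseline is the reference for behavior change is an inference, though a reasonable one: Table 2 shows no other follow-up-type behavioral survey before Month 6.

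It does not remove the conflict. Condensing a protocol into an article explains omissions, but not two incompatible meanings of enrollment. The only sentence that times the survey for a particular arm places it after enrollment, in men described as already randomized. That recruitment has closed shifts the remedy to checking and reporting.

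**Conclusion.** The point holds as a contradiction to be reconciled: the article does not fix baseline data collection relative to allocation, and part of its wording allows collection after unblinded allocation. The balance check and the behavior-change comparison would be exposed. The Poisson model would be exposed only if these values are among its covariates.

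A reader might go further and infer that the survey does follow randomization and counseling, that it follows surgery in the circumcision arm, or that the HIV rate ratio is therefore biased. The documents support none of these as fact. The abstract suggests the opposite order, the main text puts enrollment before surgery, and the source of the covariates is not stated.

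The size is unknown. The figures of about 11% and 9% rest on an assumed 10% misreporting in one arm, and the 4% to 50% range on an assumed 6-month recall and a survey taken at formal enrollment. If the timestamps show that all surveys preceded allocation, only the wording needs correcting.

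**What to change.** **Text.** Reconcile the abstract, Table 2 with footnote a, and Randomization and Follow-Up. Define enrollment once and state one order for both arms: baseline questionnaire, blood sample and swab completed before the envelope is opened. If practice differed, report the order actually followed in each arm.

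**Men already recruited.**

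- Compare web-survey timestamps with allocation dates and report survey timing by arm.
- Limit behavioral adjustment covariates to values recorded before allocation, and report the unadjusted rate ratio beside the adjusted one.
- Add a sensitivity analysis of behavior change that excludes or flags men whose survey post-dates allocation.
- Do not substitute screening-form answers for those men alone. That would mix two instruments, possibly by arm. The screening answers also decided eligibility, so using them as the reference invites regression to the mean.

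**Cost.** Wording, a timestamp check and one extra analysis, all feasible before the analysis planned for September 2023. If many surveys post-date allocation, some analyses will have fewer usable covariates or fewer men.

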### Study Measures

The baseline and follow-up surveys will collect information on sociodemographic characteristics (including age, ethnic, educational background, marital status, and monthly individual income) and sexual behaviors (including the number of male and female sex partners, frequency of vaginal or anal sex, condom use, and HIV-positive sex partners) for all enrollment participants. Follow-up surveys will be completed at 6- and 12-month follow-ups. Men randomized to receive VMMC will also be asked to complete weekly follow-up surveys for 6 weeks after VMMC to monitor for postsurgical complications, including pain, poor surgical site wound healing or infection, and premature resumption of sexual behaviors. If an adverse event is reported, trained investigators will contact participants and provide advice on whether further clinical evaluation is needed.

Fingertip blood drop samples will be collected at baseline as well as 3-, 6-, 9- and 12-month follow-ups and tested for HIV using an HIV rapid test. Venous blood samples collected at baseline as well as 6- and 12-month follow-ups will be tested for HIV, syphilis, and HSV-2. Penile swab samples will be collected at baseline as well as 6- and 12-month follow-ups and tested for HPV.

HIV rapid testing will detect antibodies against HIV-specific antigens using a solid-phase immunochromatographic assay (SD Bioline HIV/Syphilis Duo test; Standard Diagnostics Inc), and these assays will be performed at study sites. Venous blood samples will be tested for HIV using a chemiluminescent microparticle immunoassay (Anti-HIV CLIA Microparticles; Autobio Diagnostics Co) performed at Guangzhou Hybribio Medical Laboratory Limited. If a participant’s sample is found to have a positive result for HIV, we will recollect a venous blood sample from that participant and perform a confirmatory Western blot test at the local Centers for Disease Control and Prevention. Except for HIV, laboratory assays will be applied for syphilis, HSV-2, and HPV test. HPV DNA testing and genotyping was performed using the 37 HPV GenoArray Diagnostic Kit (Hybribio; Chaozhou, China). Syphilis serological tests will be performed using tolulized red unheated serum test and treponema pallidum particle assay. Detection of HSV-2 immunoglobulin G and HSV-2 immunoglobulin M in blood samples are based on a chemiluminescent microparticle immunoassay. Participants who test positive for pathogens or antibodies will be offered STI counseling and referred to a hospital for treatment.

### Participation Incentives and Follow-Up Reminders

Web-based educational materials on sexual health will be regularly posted for all participants to read via WeChat by the CoM Study’s official WeChat account. Short voluntary quizzes will be included at the end of each posted educational material, and participants who complete these quizzes will receive a CNY 2 or CNY 5 (US $0.3 or US $0.8) reimbursement. Each participant will also receive a CNY 50 (US $8) reimbursement each time they complete a questionnaire and provide a blood sample for HIV and STI testing. Participants who complete the surgery according to the study procedures will receive CNY 1000 (US $160) surgery subsidy. In addition, participants will receive an additional CNY 500 (US $80) subsidy after completing all required follow-up surveys as well as HIV and STI testing.

Reminders to complete follow-up surveys will be sent to all enrolled men via WeChat. If follow-up surveys are not completed on time, investigators will contact enrolled participants with additional reminders each week for up to 5 weeks to encourage participation and minimize loss to follow-up.

### Data Collection and Management

All data will be collected using Wenjuanxing (Ranxing Information Technology Co, Ltd [25]), a web-based questionnaire platform. Several quality-control questions will be included in the study questionnaires, and the consistency of answers will be examined by trained investigators. Information concerning identification, eligibility, baseline surveys, intervention, and follow-up surveys will be recorded in case record form. Adverse events will also be recorded. Identity information will be collected for allowance distribution purpose only, which will not be used for statistical analysis or intended for information leakage. Only study staff will be able access the study database, which will be protected with a unique log-in password that will be updated monthly to maximize data safety. The data safety monitoring committee (DSMC) of the CoM Study will be comprised of 2 statisticians, 2 clinicians, and key study investigators. The DSMC will supervise procedures, including data quality control, data integrity, data security, data sharing, and data analysis. All investigators have completed standard operating procedure training and data management training.

### Sample Size

The sample size is calculated based on the supposed protective rate of circumcision. Studies have shown that HIV incidence among MSM was 12.5/100 person-years in Chongqing [26], 15.5/100 [27] and 10.3/100 person-years [28] in Shenyang, and 15.6/100 person-years in 8 cities in China [29]. Considering participants in the CoM Study predominantly practiced insertive anal sex, consequently with lower HIV infection risk compared with those who primarily practiced receptive role, and that the effect of VMMC may be higher among men who primarily or exclusively practice the insertive anal intercourse than MSM overall, we suppose HIV incidence among MSM to be 10/100 person-years and protective rate of circumcision to be 80%, and thus, HIV incidence would be 2/100 person-years in the intervention group. A target sample size of 240 (120 in each group) is set to achieve 80% power at 1-sided α=.10, with 10% lost to follow-up.

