Sexual position preference may have a significant impact on the efficacy of VMMC to reduce HIV infection among MSM. Men who practice insertive anal sex may benefit more from VMMC than those who practice receptive anal sex. Subanalysis in a 2019 systematic review and meta-analysis [15] found that MSM who primarily engage in insertive anal sex had a 56% lower odds of HIV infection, a stronger association compared to what was found among MSM overall. In China, 70% of MSM practice either exclusively insertive anal sex or both insertive and receptive anal sex [17,18]. Thus, VMMC has the potential to become an important HIV prevention option for most MSM in China.

Only 15.3% of MSM in China have undergone circumcision [19]. This proportion is lower than the global average of 37%-39% [20]. Mainstream social conventions and religious practice in China are neutral on circumcision, neither promoting nor forbidding the procedure. Implementing a VMMC intervention in China should not be significantly hindered by Chinese traditions or cultural values. Other potentially effective interventions, such as PrEP, are still in promotion phase in China, which is impeded by high cost, low accessibility, and stigma among MSM [21,22]. As for consistent condom use, the rate of its use among MSM remains relatively low, approximately 50% [23,24]. Hence, it is essential to determine an alternative HIV prevention strategy in China. Given the high proportion of Chinese MSM who are uncircumcised and the need for alternative HIV prevention strategies in China, it is theoretically feasible to conduct an RCT to evaluate the efficacy of VMMC to reduce incident HIV infection among MSM in China. This RCT could provide valuable information to inform HIV prevention policy as well as future mathematical models and additional clinical trials of VMMC.

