### Eligibility Criteria

Individuals who meet all of the following criteria are eligible for enrolment in the CoM Study: (1) aged 18-49 years; (2) assigned male sex at birth; (3) ≥2 male sex partners and ≥10 episodes of anal sex in the past 6 months; (4) practiced insertive role in ≥7 of the last 10 episodes of anal sex with male sex partners; (5) HIV negative; (6) has foreskin that covers over half the glans when the penis is not erectile; (7) is willing to undergo VMMC; (8) resides in the city where a study site is located and has no plan to relocate in the next 12 months; (9) is willing to provide a blood sample and exfoliated penile swabs to test for HIV, HSV-2, syphilis, and HPV; and (10) is able to provide informed consent. Men who are already circumcised or enrolled in other biomedical HIV intervention studies will be excluded. Men who have been diagnosed with a bleeding disorder or have other medical contraindications to VMMC will also be excluded.

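### The 80% effect behind N=240 is unsourced and exceeds every HIV effect the protocol cites; at its own 56% figure, power is about 58%, or 32% at the 2-sided .05 level

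*Protocol article*

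**What the plan says.** All references are to the Protocol article.

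- **Control rate (Sample Size):** "we suppose HIV incidence among MSM to be 10/100 person-years".
- **Effect (Sample Size):** "protective rate of circumcision to be 80%, and thus, HIV incidence would be 2/100 person-years in the intervention group". The stated reason is that the effect may be larger in men who mainly or only take the insertive role. No source is given for the figure.
- **Size and power (Sample Size):** "A target sample size of 240 (120 in each group) is set to achieve 80% power at 1-sided α=.10, with 10% lost to follow-up".
- **Significance level (Statistical Analysis):** "A 2-sided *P* value lower than .05 will be used to infer statistically significant difference".
- **Best-matched evidence (Introduction, Overview):** "MSM who primarily engage in insertive anal sex had a 56% lower odds of HIV infection". The same section reports 50%-60% from three trials in heterosexual men, and reductions of 7% to 42% from reviews of MSM overall or by region.
- **Endpoint (Study Outcomes):** HIV incidence, not restricted by route of acquisition.
- **Entry (Eligibility Criteria, item 4):** "practiced insertive role in ≥7 of the last 10 episodes of anal sex with male sex partners", so up to 3 of the last 10 acts may have been receptive.
- **Risk by role (Sample Size):** mainly insertive men are described as "consequently with lower HIV infection risk compared with those who primarily practiced receptive role". No ratio is given.

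**The concern.** The power statement holds only for the effect it assumes. The argument for 80% is that mainly insertive men may benefit more, but the protocol already quotes an estimate for those men, and it is 56%. That estimate reflects the role preference, so the same argument cannot also carry the assumption from 56% to 80%.

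The endpoint adds to the optimism. The Introduction describes a mechanism located in the penis, while the outcome counts infections acquired in either role. Some infections are therefore probably beyond the reach of circumcision.

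The trial is presented as the first randomised evidence on this question and as an input to policy and modelling. If the true effect is near the protocol's own best-matched figure, a non-significant result is quite likely, and a reader who relies on the printed 80% power could take it for evidence of no effect.

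**Working it through.** **Inputs from the protocol.** Control rate 0.10 per person-year; 120 men per arm; 10% loss; 12 months of follow-up; 1-sided .10 (Sample Size) and 2-sided .05 (Statistical Analysis). Evaluable per arm: 120 × 0.90 = 108 men, about 108 person-years. Expected control infections: 108 × 0.10 = 10.8.

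**Step 1: reproduce the plan's figure.** For a log rate ratio from a Poisson model, n per arm = (z_α + z_β)² × (1/λ₁ + 1/λ₂) / (ln RR)².

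With λ₁ = 0.10, λ₂ = 0.02, RR = 0.20, z_α = 1.282 and z_β = 0.842: (2.123)² × (10 + 50) / (1.609)² = 104.4, so 105. Dividing by 0.90 gives 117 per arm, 234 in total, against the stated 240. The size follows from its inputs.

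**Step 2: power by effect.** Power = Φ(|ln RR| / SE − z_α), with SE = √(1/m₁ + 1/m₂) and m the expected infections per arm.

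- 80% reduction: m₁ = 10.8, m₂ = 2.16, SE = 0.745, ratio 1.609/0.745 = 2.159. At 1-sided .10: Φ(2.159 − 1.282) = 81%. At 2-sided .05: Φ(2.159 − 1.960) = 58%.
- 56% reduction: m₂ = 4.75, SE = 0.550, ratio 0.821/0.550 = 1.491. At 1-sided .10: Φ(1.491 − 1.282) = 58%. At 2-sided .05: Φ(1.491 − 1.960) = 32%.

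The brackets give the range over this Wald test, the exact and mid-P conditional tests, and a pooled two-proportion test:

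| True reduction | 1-sided .10 | 2-sided .05 |
|---|---|---|
| 80% | 81% (81-89%) | 58% (58-70%) |
| 56% | 58% (50-62%) | 32% (25-36%) |
| 50% | 51% (43-55%) | 26% (20-29%) |

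For 80% power at a 56% reduction and 1-sided .10, the Step 1 formula gives 219 per arm: 244 after loss, 488 in total. The two-proportion formula gives 428.

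**Step 3: odds or rate.** The 56% is an odds reduction. At a 10% risk the odds are 0.111; 0.44 × 0.111 = 0.049, a risk of 4.7%, which is a 53% risk reduction. Treating 56% as a rate reduction is close and slightly favours the plan.

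**Step 4: how far receptive acts limit the effect (illustrative).** If circumcision blocked every insertive infection and no receptive one, the largest all-route reduction would be s / (s + (1 − s)r). Here s is the insertive share of acts and r the receptive-to-insertive risk per act. The documents give neither the cohort's s nor r. Assumed range:

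| s | r = 1 | r = 2 | r = 3 |
|---|---|---|---|
| 0.70 (entry limit) | 70% | 54% | 44% |
| 0.85 (assumed cohort mean) | 85% | 74% | 65% |
| 0.90 (assumed cohort mean) | 90% | 82% | 75% |

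Three of the six cohort-mean cells reach 80%, but only with perfect or near-perfect protection in insertive acts.

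**The case against.** A reader might infer from the entry rule that an 80% reduction is out of reach. The documents do not support that. The 70% ceiling belongs to a man at the entry limit, not to the cohort. The average role mix and the per-act risk ratio are not given, half of the illustrative cohort-mean ceilings allow 80%, and for exclusively insertive men the ceiling is 100%. Nor does a contrast of 10 against 2 per 100 person-years imply almost no receptive infections: with perfect insertive protection, 2 of every 10 control infections could be receptive. The dilution argument shows direction only.

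Other points for the plan:

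- **Control rate.** The cited incidences run from 10.3 to 15.6 per 100 person-years. At 12.5, Wald power for 56% at 1-sided .10 would be 65%; at 15.6, 72%. Both are still below 80%, and the plan itself chose 10 because its men are at lower risk.
- **Low end of the range.** The 50% comes from a conservative exact test that is not planned. The planned Poisson model gives 58%.
- **Disclosure.** The protocol presents the effect as a supposition, calls the evidence preliminary, plans rate ratios with 95% CIs, and nowhere says that a null result will be read as no effect. This lessens the risk of misreading but does not supply power at a cited effect.
- **Timing.** Recruitment ran to July 2022, so a correction changes what is disclosed, not the design.

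None of this gives a source for 80% or closes the gap to 56%.

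**Conclusion.** The point holds as a mismatch between the assumed effect and the protocol's own evidence. The calculation is right for its inputs; the weak input is the 80%. At the 56% cited for mainly insertive men, power drops from about 81% to about 58% at 1-sided .10, and to about 32% at the 2-sided .05 level that the analysis section sets. At that level even an 80% effect has only about 58%-70%.

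This rests on 108 person-years per arm, a control rate of 10 per 100, and use of an observational odds reduction as an approximate rate reduction. The 56% may already include some receptive exposure, so it is not diluted further here. The any-route endpoint and the entry rule make 80% more optimistic; they do not exclude it.

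**What to change.** Keep n=240 and amend the Sample Size section:

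1. Beside the 80% case, state power at a 56% reduction: about 58% with the planned Poisson model (50%-62% across tests) at 1-sided .10, and about 32% (25%-36%) at 2-sided .05. Give the 80% case at 2-sided .05 as well, about 58%-70%.
2. Label 80% as an optimistic assumption above all cited estimates.
3. State that a non-significant result will not be read as absence of effect unless the 95% CI for the rate ratio excludes a 56% reduction, that is, unless its lower limit lies above 0.44.

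This needs only wording: no extra participants, data or analyses. The price is a less favourable stated power.
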